## Methods

### Trial design

TOPGUN is a randomized, open, multicenter study with an individually randomized stepped-wedge design [34] over a 24-week period to evaluate the following:Daily topical application of 1 mg/mL sirolimus solution 0.5 to 1 mL according to the size of the LMLM lesion, the experimental intervention, *versus*Usual care (no treatment), the control condition

In this design, participants are included in a cohort in which treatment is introduced at a randomized timepoint. Included participants start the intervention in a staggered fashion over time. Randomization is balanced, so each participant has the same probability of starting the intervention at a given step as any other participant over the entire study period. Four steps are planned for starting the intervention (i.e., week 0 [W0], W4, W8 and W12). Hence, 3 participants will be randomly assigned to begin the intervention on W0, 3 on W4, 3 on W8, and 3 on W12.

In order to minimize participant burden related to the follow-up visits and procedures, we tried to reduce the number of on-site visits thanks to phone calls, especially during the control period (see Tables 1, 2, 3 and 4). Similarly, blood tests may be performed in partner local laboratories, closer to patients’ homes, which will then provide results to the investigator.

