**Table 4 Tab4:**
[figure not shown]
Participant Timeline (group 4: treatment introduction at week 12)

^a^ For women of childbearing potential, until 3 months after study close-up

^b^ Drug dispensation: 3 bottles for 8 weeks (8w) or 2 bottles for 4 weeks (4w)

All patients will undergo a visit (physical, “on-the-spot” visit or via secured phoning software or phone calls, according to the step-specific participant timeline), every 4 weeks until W24, when the intervention will be stopped. Assessments before starting the intervention will be compared to those after the introduction of the intervention.

The individually randomized stepped-wedge trial design is increasingly being used in clinical practice, often in rare diseases for which patient recruitment may be difficult. Because of this very rare disease, randomizing the first topical sirolimus-treated LMLM patients seemed important to obtain high-quality evidence.

Other advantages of the stepped-wedge approach include the following [34, 35]:Each patient is his own control, hence increasing trial power with a small patient count, while taking into account a possible persisting treatment effect (contrary to cross-over designs)Being able to evaluate the effect of the time of treatment introduction and treatment duration owing to the varying treatment courses from 12 to 24 weeks.Increasing trial acceptability in this rare disease. Indeed, during the study, participants need to comply with a significantly tighter clinical follow-up than during usual care and might be reluctant to apply for trial inclusion if they believe they will not receive the experimental treatment, especially if they live far from the study center. Resorting to phone calls instead of traditional face-to-face visits also aims to address this matter.

We could not use a placebo drug because of pharmaceutical stability issues. As a result, neither the patient nor the investigator is blinded to the treatment introduction timepoint. However, the main outcome will be assessed on photographs by an independent blinded adjudication committee.

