#### Intervention

During the observation (control) period, patients will receive usual care for their LMLM, which is no treatment at this stage of the condition.

Then, after crossing over to the experimental period, the intervention is the 1-mg/mL sirolimus oral solution (Rapamune®, Pfizer), administered once daily. If the LMLM covers below an estimated <4 cm^2^ of target area, the treatment dose is 0.5 mL, once daily. If the LMLM covers above an estimated ≥4 cm^2^ of target area, the treatment dose is 1 mL, once daily.

A total of 0.5 or 1 mL non-diluted sirolimus solution will be taken from the bottle by using the 1-use dosing syringe and applied on a standardized disposable applicator device. Then the applicator device will be gently applied, only on the LMLM, until the solution is no longer oozing from the applicator device, for at least 10 s. The patient must then not eat, drink, brush teeth, or use mouthwash for 1 h.

Applicators and syringes are to be disposed of adequately. Rapamune® bottles must be brought at every dispensation visit to assess patient observance. Syringes must not be re-used.

The treatment will be started at a randomized timepoint (W0, W4, W8, or W12) and will be taken until W24 whatever the starting time.

In case of serious adverse reactions, including local necrosis or any systemic reaction, the intervention (topical sirolimus) will be stopped. In case of local side effects, the intervention might be temporarily halted. If the patient, the sponsor, and the investigator deem it appropriate, the intervention can be resumed, at full or half-dose. In case of relapse, the lowest bearable dose will be sought; otherwise, the treatment might be stopped. If the lesion is totally removed before W24, the investigator could propose early withdrawal of the treatment. In this setting, follow-up would be according to the protocol until W24.

Participants (or together with their parents if they are < 18 years old) will be asked to keep a daily participant diary, recording information about adherence and safety data. They will be asked to bring the diary at each study visit.

At each on-site study visit, participants will be asked to provide all their used and unused study drug containers.

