##### Secondary outcomes

Secondary outcomes will assess topical sirolimus efficacy and safety. They include investigator- and patient-reported outcomes, with an emphasis on quality of life and symptoms.Investigator-assessed PGA at weeks 0, 4, 8, 12, 16, 20, and 24Patient-assessed oozing, bleeding, sialorrhea, eating impairment, taste modification, aesthetic impairment, pain, and global discomfort, each on a numeric scale from 0 to 10 (0, clear; 10, very severe), at weeks 0, 4, 8, 12, 16, 20, and 24Global evolution assessed by the patient from −10 to 10 (−10, severe worsening; 0, no change; 10, complete recovery), at weeks 4, 8, 12, 16, 20, and 24Quality of life assessment (cDLQI for patients 5 to 16 years or DLQI > 16 years), at baseline, treatment introduction visit and W24Measurement of the lesion (length, width, thickness) by the investigator, at baseline, treatment introduction visit and W24Time to obtain optimal results (i.e., time from treatment introduction visit to time reaching the minimal PGA score)

Reported side effects with oral sirolimus treatment include fatigue, headache, oral mucositis, hypertension, dyslipidemia, hyperglycemia, cytopenia, and infections [nadal2016]. Topical application of sirolimus in oral diseases has also been tied to local irritation and pain [Soria2009]. Hence, to account for these reported adverse effects, safety assessments will be both clinical and biological. The clinical surveillance will include the recording of clinical local and general side effects according to the daily completion of the patient follow-up diary, questions from the investigator at each visit and physical examination and blood pressure measurement at each on-the-spot visit. Participants will also be weighed at each on-the-spot visit.

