#### Participant timeline

The duration of participation is 24 weeks for each patient, whatever the step they are randomized in. The participant timeline encompasses general and step-specific schedules, which are described in Tables 1, 2, 3 and 4. Even if the intervention is stopped early, whatever the reason, any assessment planned should be performed, including blood draws, phone calls and study center visits.

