Time to optimal results will be described with median and interquartile range. Safety data will be reported using descriptive analysis.

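### Time to optimal results, defined as time to the lowest PGA, is a poor measure of speed of response: participants who never improve still get a time, usually a short one, and the longest possible time depends on the randomised group

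*Protocol article*

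**What the plan says.** Under Secondary outcomes, the last efficacy item is the time "to obtain optimal results (i.e., time from treatment introduction visit to time reaching the minimal PGA score". The Statistical methods section fixes the summary: "Time to optimal results will be described with median and interquartile range". Neither place asks for an improvement, says how a participant without one is counted, or treats the end of follow-up as censoring. The text also does not say whether the blinded committee's PGA or the investigator's PGA is meant; both are collected every 4 weeks.

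Three design statements bear on it. The Intervention section says: "The treatment will be started at a randomized timepoint (W0, W4, W8, or W12) and will be taken until W24 whatever the starting time". The Participant timeline says: "The duration of participation is 24 weeks for each patient, whatever the step they are randomized in". The Trial design section gives the allocation, "3 participants will be randomly assigned to begin the intervention on W0, 3 on W4, 3 on W8, and 3 on W12", and presents the "varying treatment courses from 12 to 24 weeks" as an advantage of the design.

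**The concern.** Every series of scores has a lowest value, so on the natural reading every participant contributes a time whether or not the lesion improved. With a flat or worsening PGA the lowest value is the first one counted, so a treatment failure gets the shortest time on offer. Someone who improves slowly keeps reaching new lows until follow-up ends, and follow-up after introduction ends earlier in the groups that start later.

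A reader will take a short time to optimal results as a sign of a fast-acting drug. Under this definition a short median can equally come from participants who did not respond, and slow responders' times depend partly on the group they were randomised to.

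**Working it through.** **Inputs from the protocol article.** Start at W0, W4, W8 or W12, with treatment and participation ending at W24 (Intervention; Participant timeline). Three participants per group, 12 in all (Trial design). PGA is an integer from 0 to 5 (Data collection methods), read every 4 weeks (Statistical methods). A 1-point improvement versus baseline is called clinically relevant (Primary outcome). No SD, effect size or trajectory is given; those used below are assumptions.

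**Follow-up after introduction** = 24 − start week:

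| Group | Start week | Weeks after introduction | Readings after introduction |
|---|---|---|---|
| 1 | 0 | 24 | 6 |
| 2 | 4 | 20 | 5 |
| 3 | 8 | 16 | 4 |
| 4 | 12 | 12 | 3 |

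This reproduces the stated range of 12 to 24 weeks. The third column is also the longest time each group can record.

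**Without rating noise** (time = first visit at which the participant's own lowest PGA occurs):
- Flat or worsening PGA: 0 weeks in every group, or 4 if the introduction visit is not counted.
- Lowest score first reached at W24 in everyone: 24, 20, 16 and 12 weeks, three participants each. The median is (16 + 20)/2 = 18, with interquartile range 15 to 21.
- A mixture of such continuing responders and flat non-responders, allocated at random, with the introduction visit counted: the average median is 0 weeks with 0 or 3 responders of 12, about 6.2 with 6, about 15.4 with 9, and 18 with 12. The statistic lengthens as more participants benefit.

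**With rating noise** (assumed: baseline mean 3, between-person SD 0.8, within-person SD 0.3 to 0.8, scores rounded to integers, 20,000 simulated participants per group):

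| Scenario | Result |
|---|---|
| Inert drug, introduction visit counted | pooled median 0 to 4 weeks |
| Inert drug, introduction visit not counted | pooled median 4 to 8 weeks |
| 2-point benefit building over 12 weeks | pooled median 12 weeks |
| 2-point benefit building over 24 weeks | mean about 16-19 weeks (group 1) to about 7-8 weeks (group 4) |

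In the last row at SD 0.5, with the introduction visit counted, the group means are 17.6, 14.0, 10.4 and 6.9 weeks, although the drug acts at the same speed in all four groups.

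**The other reading.** If the minimal score means PGA 0 (clear), a participant who does not clear has no time. With no censoring, the median then covers only those who clear.

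**Check of the remedy.** Take time to a first fall of 1 point or more from the introduction visit. A noise-free responder losing 3 points steadily over 24 weeks falls 3/24 = 0.125 points a week and reaches 1 point at 1/0.125 = 8 weeks in every group. A flat non-responder is censored at 24, 20, 16 or 12 weeks instead of scoring 0 or 4. With noise, one unconfirmed 1-point fall still marks about 45% of inert-drug participants as improved by 12 weeks at SD 0.5 (30% to 56% for SD 0.3 to 0.8), which is why confirmation is worth adding.

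**The case against.** The strongest reply is that a detailed analysis plan is announced and a journal article need not carry derivation rules such as ties, censoring or whether the introduction visit counts. That stands for those details. It does not cover the definition and summary, which are stated here; a response condition or censoring would change the outcome rather than fill in a gap.

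The second reply is that the harm is small. The outcome is descriptive, has no comparator, and sits beside the model-based effects at each duration of treatment and a plot of every participant's PGA. With 12 participants, flat courses will be visible. This also stands, and it limits how serious the point is.

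Third, a reader might infer more than the text supports: that non-responders always score the shortest times, that continuing responders score exactly the follow-up their group allows, and that the median is fixed at 18 weeks by design. These hold only without noise and, for the last two, only if the lowest score is first reached at W24. In the simulated 24-week benefit at SD 0.5, only about 28-31% of participants per group score their full follow-up, and the pooled median is 12 weeks. With noise some non-responders score longer times. A fast responder (2 points within 4 weeks) has a median of 4 weeks, the same as the inert drug at that SD. If everyone responded and levelled off well within 12 weeks, the measure would carry real information on speed.

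**Conclusion.** The point holds as a defect of definition in a secondary outcome and should be corrected. Two consequences follow from the protocol's wording alone if the participant's own lowest score is meant: a PGA that never improves yields 0 or 4 weeks in the absence of noise, and the attainable time is capped at 24, 20, 16 or 12 weeks by allocation. The simulated sizes (inert median 0 to 8 weeks against 12; group means from about 16-19 down to about 7-8 weeks) rest on assumed SDs and trajectories, but the direction is the same across the range tried.

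It would go too far to say that the statistic reflects only the schedule and rating noise, or that the trial would rank an inert drug above an effective one: allocation shifts slow responders' times without fully determining them, and no such drug comparison is planned. The primary analysis at 12 weeks after introduction is not touched. Reading the minimum as PGA 0 leaves a different defect, since an uncensored median would then describe only those who clear.

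**What to change.** Changes to the definition and its summary:
- State which PGA is used, preferably the blinded committee's.
- Redefine the outcome as time from treatment introduction to the first improvement of at least 1 point from the introduction-visit value, preferably confirmed at the next visit. Say that this reference is the pre-treatment value; for groups 2 to 4 it differs from the baseline against which the protocol calls 1 point relevant.
- Say how a fall first seen at the last visit is handled. Group 4 has no reading after 12 treated weeks, so such a fall cannot be confirmed there; the rule should be the same in all groups.
- Censor participants without the event at their last assessment (W24) and report a Kaplan-Meier curve and median.
- Add the proportion improved by 12 weeks of treatment, the exposure common to all groups.

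If time to the lowest PGA is kept, report it only descriptively, among participants who improved by at least 1 point and within the first 12 treated weeks, alongside the number who did not improve.

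The cost is a small amendment to a secondary outcome, using PGA readings already scheduled. The Trial status section reports five participants included and two completed, so the change should be dated and disclosed. The new outcome also answers a somewhat different question: first response rather than best response.

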#### Participant timeline

The duration of participation is 24 weeks for each patient, whatever the step they are randomized in. The participant timeline encompasses general and step-specific schedules, which are described in Tables 1, 2, 3 and 4. Even if the intervention is stopped early, whatever the reason, any assessment planned should be performed, including blood draws, phone calls and study center visits.

#### Sample size

We could not define a reasonable effect-size hypothesis because LMLM is a very rare disease, with currently no described pharmaceutical treatment for LMLM. Hence, we did not perform any sample size calculation.

#### Recruitment

Both children > 5 years old and adults are recruited alike in TOPGUN because LMLMs can be found at every age. The University hospital of Tours is a tertiary reference center for cutaneous vascular anomaly care, which all investigators are involved in. We also reached out to other university hospital centers in the “Grand-Ouest” region in France and the Necker-Enfants Malades pediatric hospital, located in Paris (authorization granted in January 2021).

### Methods: Assignment of interventions

#### Allocation

##### Sequence generation and allocation concealment mechanism

Time of cross-over to the intervention will be randomly assigned to the patient at W0, W4, W8, or W12 with a 1:1:1:1 ratio allocation as per a computer (SAS-based)-generated randomization schedule. Participants will be randomized by using Ennov Clinical, an online central randomization procedure. To ensure allocation concealment, randomization will not be possible until the participant has been recruited into the trial, especially with all selection criteria collected and met.

##### Implementation

The allocation sequence will be generated by a statistician not involved in the recruitment or follow-up of participants.

#### Blinding

We could not use a placebo drug because of pharmaceutical stability issues. Sirolimus oral solution is stable for < 30 days after opening. A recondition in unlabeled study bottles, which would be the *sine qua non* condition to consider a placebo drug, would have required very frequent treatment deliveries, which did not fit with our monthly stepped-wedge design and would have sharply increased study costs. As a result, neither the investigators nor participants will be blinded and there will be no placebo intervention. Both the patient and the investigator will be aware of his/her allocated time of cross-over to intervention. However, the adjudication committee, which will assess the primary outcome, will be blinded to treatment allocation by the use of standardized anonymized photographs.

### Methods: Data collection, management, and analysis

#### Data collection methods

LMLMs are a rare skin disease for which neither evaluation guidelines nor purposely developed evaluation instruments exist. The PGA scale is a tool widely used in dermatology. It represents a global evaluation of disease severity. We use a 6-point PGA scale: 0, clear; 1, almost clear; 2, mild; 3, moderate; 4, severe; 5, very severe. The PGA scale is widely used in psoriasis but is also used in a wide array of skin diseases [37, 38] and as an easily obtainable global evaluation of disease severity is an interesting tool. The DLQI and cDLQI are widely used instruments to assess health-related quality of life in dermatology. The cDLQI is validated for children from age 4 years up to 16 years [35].

Study staff with their own access right to the study database will enter/capture data from source documents corresponding to a participant into the protocol-specific electronic Case Report Form (eCRF). All information required by the protocol will be entered in the eCRF, and an explanation will be provided for each missing piece of information. The data must be collected as they are obtained and transcribed into these forms in a clear manner. If a correction is required for an eCRF, the time and date stamps track the person entering or updating eCRF data and create an electronic audit trail.

The participant will be given detailed contact information of their study center. In case of tolerance issues or difficulty to perform intervention procedures or self-reported outcomes collection, participants will be instructed to reach out to the study center. Any information needed will be provided, and additional unplanned visits may be organized if deemed necessary.

In case of loss of follow-up or missing data, study personnel may reach out to the participant to try to recover missing information or replan missed eventual study visits.

#### Data management

Data management will be performed by the INSERM CIC-P 1415. An eCRF will be developed by using the Ennov Clinical software. eCRF management will be performed in agreement with the INSERM CIC-P 1415 Standardized Operating Procedures (SOP). The Clinical Research Associate in charge of the study will be trained in the eCRF and will be in charge of the investigator training. Data will be entered in investigating centers via a secure web site, monitored by Clinical Research Associates and potential queries will be edited by data managers, in agreement with a prespecified data management plan.

Data will be reviewed before the database is locked. The database will be locked in agreement with the INSERM CIC-P 1415 SOPs, and data will be extracted in a SAS or other format according to statistical requirements.

#### Statistical methods

A detailed analysis plan will be a priori defined. SAS 9.4 and R 3.3.1 (or latest versions) will be used for analysis. The level of statistical significance will be set at 5%.

The primary outcome (PGA) will be treated as a continuous variable. For analysis, we will use the model described by Hooper et al. [35] Analysis will rely on a mixed linear regression model with a random effect for participant. For each participant, we will include the 7 PGA measurements from W0 to W24 (assessed every 4 weeks).

The model will be as follows, denoting *Y*_*ijt*_ as the PGA for individual *i* = 1,.., n in sequence *j* = 1,…, T at time *t* = 0,…, *T* after randomization:$${Y}_{ij t}=\beta +{\tau}_t+{A}_{jt}+{\eta}_{ij}+{\varepsilon}_{ij t}$$

where $${\eta}_{ij}\sim N\left(0,{\sigma}_b^2\right)$$ is the participant random effect; $${\varepsilon}_{ijt}\sim N\ \left(0,{\sigma}_w^2\right)$$ is the random error; and *η*_*ij*_ and *ε*_*ijt*_ are all independent, and,$${A}_{jt}\left\{\begin{array}{c}0\ if\ sequence\ j\ is\ in\ the\ control\ condition\ at\ time\ t\\ {}{\alpha}_k if\ sequence\ j\ crosses\ to\ the\ intervention\ between\ times\ t-k\ and\ t-k+1,k\ge 1\end{array}\right.$$

The mean of PGA for an individual participant follows a trajectory with baseline *β* (mean PGA at baseline) and time effects *τ*_*t*_, *t* = 0,…,6 with *τ*_0_ = 0.

When the participant crosses over to topical sirolimus, additional effects of treatment will be estimated with *α*_1_ additional treatment effect in the first 4-week period after crossing over, changing to *α*_2_, *α*_3, …,_
*α*_6_, mean additional treatment effect at W8, W12, W16, W20, and W24 after the introduction of sirolimus respectively.

This trial has a 4-sequence design, and our primary treatment effect of interest will be α_3_, the mean difference in PGA at 12 weeks after the introduction of topical sirolimus. We will also estimate *α*_1_, *α*_2_, *α*_4_, *α*_5_, and *α*_6_, mean additional treatment effects at W4, W8, W16, W20, and W24, respectively, after the introduction of sirolimus.

Missing data will not be imputed for this analysis.

Individual trajectories of PGA will be plotted by using a spaghetti plot.

Secondary outcomes (global severity of disease and functional impairments) will be treated as continuous variables ranging from 0 to 10. We will use the same model as for the primary outcome.

Time to optimal results will be described with median and interquartile range. Safety data will be reported using descriptive analysis.

